## Statistical Analysis Plan Amendments

| SAP version number | Date Approved | Protocol version number† | Section number changed | Description of and reason for change | Timing of change with respect to interim/final analysis | Blind Reviewer |  |
|--------------------|---------------|--------------------------|------------------------|--------------------------------------|---------------------------------------------------------|----------------|--|
|                    |               |                          |                        |                                      |                                                         | Name:          |  |
|                    |               |                          |                        |                                      |                                                         | Signature:     |  |
|                    |               |                          |                        |                                      |                                                         | Date:          |  |
|                    |               |                          |                        |                                      |                                                         | Name:          |  |
|                    |               |                          |                        |                                      |                                                         | Signature:     |  |
|                    |               |                          |                        |                                      |                                                         | Date:          |  |
|                    |               |                          |                        |                                      |                                                         | Name:          |  |
|                    |               |                          |                        |                                      |                                                         | Signature:     |  |
|                    |               |                          |                        |                                      |                                                         | Date:          |  |

† This SAP was written based on information contained in the trial protocol version as listed here.

| Abbreviations & Definitions                    |                                                                                                                                                                |
|-----------------------------------------------------------|----------------------------------------------------------------------------------------------------------------------------------------------------------------|
| Abbreviation / Acronym                             | Meaning                                                                                                                                                 |
| BCTU                                                      | Birmingham Clinical Trials Unit                                                                                                                                |
| BMI                                                       | Body Mass Index                                                                                                                                                |
| BSG                                                       | British Society of Gastroenterology                                                                                                                            |
| CONSORT                                                   | Consolidated Standards of Reporting Trials                                                                                                                     |
| CRF                                                       | Case Report Form                                                                                                                                               |
| CTCAE                                                     | Common Terminology Criteria for Adverse Events                                                                                                                 |
| DMC                                                       | Data Monitoring Committee                                                                                                                                      |
| ICA-AKI                                                   | International Club of Ascites - Acute Kidney Injury                                                                                                            |
| ISRCTN                                                    | International Standard Randomised Controlled Trial Number                                                                                                      |
| ITT                                                       | Intention to Treat                                                                                                                                             |
| QALY                                                      | Quality-adjusted Life Year                                                                                                                                     |
| SAE                                                       | Serious Adverse Event                                                                                                                                          |
| SAP                                                       | Statistical Analysis Plan                                                                                                                                      |
| SUSAR                                                     | Suspected Unexpected Serious Adverse Reaction                                                                                                                  |
| TSC                                                       | Trial Steering Committee                                                                                                                                       |
| Term                                               | Definition                                                                                                                                              |
| International Standard Randomised Controlled Trial Number | A clinical trial registry                                                                                                                                      |
| Protocol                                                  | Document that details the rationale, objectives, design, methodology and statistical considerations of the study                                               |
| Randomisation                                             | The process of assigning trial participants to intervention or control groups using an element of chance to determine the assignments in order to reduce bias. |
| Statistical Analysis Plan                                 | Pre-specified statistical methodology documented for the trial, either in the protocol or in a separate document.                                              |

## 1. Introduction

This document is the Statistical Analysis Plan (SAP) for the CALIBRE trial, and should be read in conjunction with the current trial protocol. This SAP details the proposed analyses and presentation of the data for the main paper(s) reporting the results for the CALIBRE trial.

The results reported in these papers will follow the strategy set out here. Subsequent analyses of a more exploratory nature will not be bound by this strategy, though they are expected to follow the broad principles laid down here. The principles are not intended to curtail exploratory analysis (e.g. to decide cut-points for categorisation of continuous variables), nor to prohibit accepted practices (e.g. transformation of data prior to analysis), but they are intended to establish rules that will be followed, as closely as possible, when analysing and reporting data.

Any deviations from this SAP will be described and justified in the final report or publication of the trial (using a table as shown in Appendix A). The analysis will be carried out by an appropriately qualified statistician, who should ensure integrity of the data during their data cleaning processes.

## 2. Background and rationale

The background and rationale for the trial are outlined in detail in the protocol. In brief, liver disease is the 5th largest cause of death in the UK, with mortality predicted to double in 20 years. Patients with liver disease die younger with the average age of death of 59 years, compared with 82-84 years for heart and lung disease and stroke. In England, in total 30,000–60,000 patients are at risk or affected by liver cirrhosis. One of the major complications of cirrhosis is portal hypertension and variceal bleeding. In patients with cirrhosis, varices develop at a rate of 5% per year with 10 year cumulative incidence of 44%. At least 3,000 patients are admitted to hospital in England per year with variceal bleeding, with inpatient mortality of 15% and one year mortality of up to 40%.

At present there are two options for primary prevention of variceal bleeding, namely non-selective beta-blockers and variceal band ligation. There have been two important guidelines published in the UK in 2015-2016 from NICE and the British Society of Gastroenterology (BSG). NICE favours banding for primary prevention, whereas the British Society of Gastroenterology (BSG) suggests banding if intolerant of beta-blockers. A large randomised controlled trial would help clinicians decide which the better treatment for primary prevention is as the current evidence is based on underpowered and low quality trials. Beta-blockers used for portal hypertension in the UK are propranolol and carvedilol. Carvedilol is better tolerated and therefore has been selected as the beta-blocker for this trial. If carvedilol is found to be superior to variceal band ligation then it will become first line therapy in primary prevention.

### 3. Trial objectives

The primary objective is to compare carvedilol versus variceal band ligation with respect to variceal bleeding within 1 year of randomisation in participants with cirrhosis and medium to large oesophageal varices that have never bled.

Secondary objectives are as follows:

- To investigate the effect of carvedilol and variceal band ligation on survival, development of other complications of cirrhosis and adverse events.
- To assess cost-effectiveness, participant preference and use of alternative or cross over therapies.

### 4. Trial methods

#### 4.1. Trial design

CALIBRE is a multicentre, pragmatic, randomised controlled, open-label, two arm parallel group trial with an internal pilot. Approximately 66 Acute NHS Trust/Health Boards in the UK will be open to recruitment. Participants will be recruited from secondary care in one of three ways; in routine variceal surveillance endoscopy; referral from an outpatient clinic following a diagnostic endoscopy; and identification from inpatient referrals. See Appendix B for trial schema.

Due to the very different nature of the two interventions under study (drug versus endoscopic variceal band ligation), it is not feasible to have a blinded design. There are treatment implications for the participants following their allocated procedure and therefore the research staff need to be aware of the intervention received.

#### 4.2. Trial interventions

##### Carvedilol

Participants will be prescribed 12.5mg once daily (od) for up to 12 months. They will be seen in a follow up clinic at four weeks to assess for any short term adverse events such as symptomatic hypotension, gastrointestinal side effects like nausea, and shortness of breath. These participants will not be offered routine endoscopic surveillance, as per standard of care.

##### Variceal Band Ligation

The procedure will be performed as per the British Society of Gastroenterology guidelines. Varices are banded at regular intervals (usually two to four weekly) until they are eradicated when they are normally replaced by scar tissue or by varices of much smaller size. Participants usually require on average 2-3 banding procedures to achieve eradication. After successful eradication of the varices, participants have a repeat endoscopy at approximately three

months, then at approximately six monthly thereafter. Any recurrent varices (i.e. medium to large varices) are treated with further variceal band ligation until eradication and then offered repeat endoscopy at approximately six monthly intervals.

### **4.3. Primary outcome measure**

The primary outcome is any variceal bleeding within 1 year of randomisation.

### **4.4. Secondary outcome measures**

The secondary outcomes are as follows:

- Time to first variceal bleed in days (from randomisation).
- Mortality at one year (from randomisation):
  - All-cause mortality
  - Liver related mortality
  - Cardiovascular mortality.
- Transplant free survival at one year (from randomisation).
- Adverse events related to treatment (up to 12 months after randomisation):
  - Dysphagia requiring discontinuation of treatment
  - Symptomatic hypotension requiring change in treatment
  - Dyspnoea
  - Gastrointestinal upset.
- Other complications of cirrhosis:
  - New onset ascites confirmed clinically or on imaging and graded as per ICA recommendations.
  - New onset encephalopathy defined using West Haven Criteria.
  - Spontaneous bacterial peritonitis
  - Hepatocellular carcinoma
  - Any renal dysfunction as per International Club of Ascites – Acute Kidney Injury (ICA-AKI) definitions.
- Health-related quality of life (EQ-5D-5L) from randomisation to six and 12 months.
- Use of healthcare resources, costs and cost-effectiveness based on the outcomes of cost per variceal bleeding avoided within one year of randomisation, cost per Quality-adjusted Life-year (QALY) estimated using the EQ-5D-5L, and cost per death avoided at 1 year.
- Participant preference (via qualitative interviews in the pilot study). This qualitative data will complement quantitative outcome assessment.
- Use of alternative therapies.
- Crossover therapies.

### **4.5. Timing of outcome assessments**

The schedule of trial procedures and outcome assessments are given in protocol section 8.3.

## 4.6. Randomisation

Participants will be randomised in a 1:1 ratio to either carvedilol or variceal band ligation.

Randomisation will be performed centrally at the Birmingham Clinical Trials Unit (BCTU) using a minimisation algorithm incorporating the following factors:

- Presence or absence of hepatic decompensation (ascites or encephalopathy)
- Size of the largest varix (Grade II, or Grade III)
- Age of the participant at randomisation (18-50, 51-70, >70)
- Presence or absence of alcohol related liver disease

A 'random element' will be included in the minimisation algorithm, so that each participant has a probability (unspecified here), of being randomised to the opposite intervention that they would have otherwise received. Full details of the algorithm used will be stored in a confidential document at BCTU.

## 4.7. Sample size

The sample size calculation has been based on published data from both a Cochrane meta-analysis of variceal banding versus beta-blockers and data from the first UK randomised trial of carvedilol published in this disease area. The Cochrane meta-analysis reported an overall 1-year variceal bleeding rate of 12% in the variceal banding ligation group. The 1-year bleeding rate was chosen for the primary outcome as Kaplan-Meier curves suggest that the majority of variceal bleeding occurs in the first year after treatment. In order to detect a 33% proportional difference in variceal bleeding rates (i.e. from 12% to 8%, a 4% absolute difference) between groups using a 2-sided test for comparison of proportions with a 1:1 allocation ratio, 90% power and a type I error rate of 5% (i.e.  $\alpha=0.05$ ), requires 2362 participants (1181 per group). Assuming and adjusting for a 10% attrition/loss to follow-up rate (based on the similar patient population studied), which is thus a conservative estimate due to our shorter duration of follow-up), increases the required sample size to 2630 participants in total (1315 per group).

## 4.8. Framework

The objective of the trial is to test the superiority of one intervention to another.

The null hypothesis is that there is no difference in the 1-year variceal bleeding rate between the intervention groups. The alternative hypothesis is that there is a difference between the groups.

## 4.9. Interim analyses and stopping guidance

A separate Data Monitoring Committee (DMC) reporting template will be drafted and agreed by the DMC. Interim analyses of major outcomes and safety data will be conducted and provided in strict confidence to the DMC. The statistical methods stated in this SAP will be followed for the outcomes included in the DMC report, where possible.

The DMC will operate in accordance with a trial specific charter based upon the template created by the Damocles Group. The DMC will meet at the end of the 12 months internal pilot trial to assess the safety data, as part of the planned interim analysis and give advice on continuation to the main trial (see Section 4.10). Since this is an internal pilot trial, and these safety data will be included in the main analysis of the CALIBRE trial, these data will remain confidential, except to members of the DMC and the trial statistician(s) performing the analysis.

During the main trial, the DMC will meet at least annually, or as per a timetable agreed between the DMC prior to trial commencement. Data analyses will be supplied in confidence to the DMC, which will be asked to give advice on whether the accumulated data from the trial, together with the results from other relevant research, justifies the continuing recruitment of further participants. The DMC will advise the chair of the TSC if, in their view, any of the randomised comparisons in the trial have provided both (a) “proof beyond reasonable doubt” that for all, or for some, types of participant one particular treatment is definitely indicated or definitely contraindicated in terms of a net difference in the major outcomes, and (b) evidence that might reasonably be expected to influence the patient management of many clinicians who are already aware of other main results. The TSC can then decide whether to close or modify any part of the trial.

#### **4.10. Internal Pilot Progression Rules**

At the end of the 12-month pilot phase, the following targets should be met to justify progression to the main trial:

- Minimum of 250 participants recruited across the 20 sites with 2 sites opening per month and an average of 1.6 participants per month per open site.
- 90% of participants complete data collection at their six months follow-up visit.
- Trial Steering Committee and Data Monitoring Committee report no safety concerns which would prohibit continuation to the main trial.

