## Appendix C: Schedule of assessments

**Table of Assessments**

|                                                     | Randomisation
and Baseline | 4 weeks ‡ ± 1
week
FU visit | 6 months ± 2
months FU visit | 12 months ± 2
months FU visit |
|-----------------------------------------------------|-------------------------------|----------------------------------------------|---------------------------------|----------------------------------|
| Confirm eligibility                                 | ✓                             |                                              |                                 |                                  |
| Seek informed consent                               | ✓                             |                                              |                                 |                                  |
| Randomisation                                       | ✓                             |                                              |                                 |                                  |
| Medical history #                        | ✓                             |                                              |                                 |                                  |
| Medication review                                   | ✓                             | ✓                                            | ✓                               | ✓                                |
| Physical examination                                | ✓*                            |                                              | ✓*                              | ✓*                               |
| Office blood pressure                               | ✓                             | ✓                                            | ✓                               | ✓                                |
| Pulse                                               | ✓                             | ✓                                            | ✓                               | ✓                                |
| Standard care blood tests                           | ✓*                            |                                              | ✓*                              | ✓*                               |

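### The pilot recruitment target of 250 does not follow from 20 sites, 2 openings per month and 1.6 participants per site-month, which give 240

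*SAP*

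**What the plan says.** SAP section 4.10 (Internal Pilot Progression Rules) introduces its criteria with "At the end of the 12-month pilot phase, the following targets should be met to justify progression to the main trial". The first criterion puts four numbers in one sentence: "Minimum of 250 participants recruited across the 20 sites with 2 sites opening per month and an average of 1.6 participants". The rate is monthly, for each open site. The lead-in supplies a fifth number, the 12-month duration.

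The second criterion is "90% of participants complete data collection at their six months follow-up visit". It does not say which participants form the denominator. Appendix C gives the window for that visit as 6 months ± 2 months. The third criterion concerns safety and is not at issue here.

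Section 4.9 adds that the DMC meets at the end of the pilot and gives advice on continuing to the main trial.

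**The concern.** The number of sites, the opening schedule, the rate per open site and the duration together determine expected recruitment. The participant target in the same sentence should follow from them, and it does not: the stated inputs give fewer participants than the stated minimum.

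These are the pre-specified criteria for progressing to the main trial. If a pilot can meet its site and rate targets and still miss its participant target, the committees must decide afterwards, with the result in front of them, which number governs. Pre-specified progression criteria are meant to avoid that.

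**Working it through.** **Inputs (all SAP section 4.10):** 12 months; 2 sites opening per month; 20 sites; 1.6 participants per month per open site; target 250.

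**Formula.** Expected recruitment = rate × site-months, where site-months are the sum over months 1 to 12 of the number of open sites. With a cap of 20, open sites in month m = min(20, 2m). This assumes that no site is open before month 1 and that each pair opens at the start of its month.

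**Attempt to reproduce 250 with 20 sites.** The cap is reached in month 10.
- Site-months: 2 + 4 + 6 + 8 + 10 + 12 + 14 + 16 + 18 + 20 + 20 + 20 = 150.
- Recruitment: 150 × 1.6 = 240.
- Shortfall: 250 − 240 = 10, which is 10/250 = 4%.

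**Could rounding of the rate explain it?** A rate that rounds to 1.6 is below 1.65, and 150 × 1.65 = 247.5, so recruitment stays under 247.5. The rate needed is 250/150 = 1.67.

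**What does give 250?** If two sites open every month for the full 12 months, there are 24 sites at the end.
- Site-months: 2 + 4 + … + 24 = 156.
- Recruitment: 156 × 1.6 = 249.6, which rounds to 250.

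This suggests that the target was built on 24 sites with start-of-month opening, and that the site count is the likelier slip. The document does not confirm this.

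**Effect of chance.** If the recruitment count is taken as Poisson (an assumption; the SAP gives no distribution), the probability of reaching 250 is about 27% with mean 240, against about 50% with mean 249.6.

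**The 90% criterion.** On the same 20-site schedule, the numbers with enough follow-up at month 12 are:

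| Point in the visit window | Recruited by | Site-months | Participants | Share of 240 |
|---|---|---|---|---|
| Earliest edge (4 months) | month 8 | 72 | 115.2 | 48% |
| Nominal (6 months) | month 6 | 42 | 67.2 | 28% |
| Latest edge (8 months) | month 4 | 20 | 32 | 13% |

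The denominator therefore depends on what counts as having reached the visit.

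**The case against.** **240 is not a ceiling.** A reader might infer that 240 is the most the stated plan can deliver. The SAP does not say how many sites are open when the pilot clock starts. One site already open gives 3 + 5 + … + 19 + 20 + 20 + 20 = 159 site-months and 254.4 participants; two give 168 and 268.8. The document mentions no such head start, but it does not exclude one. This stands: the shortfall is conditional on starting from zero.

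**A larger shortfall is not supported.** Mid-month or end-of-month opening would give 140 or 130 site-months, hence 224 or 208 participants, and one might quote a gap of up to 42. But under those conventions the 24-site schedule gives only 230.4 or 211.2, so neither reproduces the plan's 250. The supportable gap is 10.

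**The 90% criterion is not a second contradiction.** A reader might infer that it cannot be met, because most participants are not yet due a six-month visit at month 12. That holds only if the denominator is everyone recruited. The wording refers to participants at their own six-month visit, and a committee would naturally count those who have reached it. Nor are only those randomised by month 6 assessable: the ± 2-month window admits visits from 4 months, so about 115 of 240 could have been seen. It is also no defect that a true rate equal to the threshold passes only about half the time. What remains is an unstated denominator.

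**The consequence is limited.** Section 4.10 says the targets should be met to justify progression; it states no automatic stop. A committee could reasonably accept a 4% miss. This also stands, and it limits the weight of the point without removing the disagreement between the figures.

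**Conclusion.** The recruitment criterion in section 4.10 is internally inconsistent. Starting from zero sites, with opening at the start of each month, its inputs give 240 participants against a minimum of 250: a gap of 10 (4%), or 1.60 against 1.67 per site-month. The target is reproduced with 24 sites rather than 20. A pilot exactly on its site and rate targets would miss its participant target.

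The point rests on there being no sites open before month 1, which the SAP neither states nor rules out. It concerns the pilot progression decision only. The main sample size, the primary analysis and the type I error are untouched. The 90% criterion needs a clarifying phrase and would not be a finding by itself.

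**What to change.** Make the numbers in the first criterion of section 4.10 agree, in one of these ways:
- 24 sites with a target of 250 at 1.6 per site-month;
- 20 sites with a target of 240 at 1.6;
- 20 sites with a target of 250 and a rate of 1.67;
- the present figures, with a statement of how many sites are already open at the start, if that is what was planned.

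The sponsor should choose according to what was planned; the arithmetic alone does not show which figure is wrong.

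As a minor clarification, state that the 90% completion criterion applies to participants who have reached their six-month visit by the assessment date, and say how the ± 2-month window is used to decide that.

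The cost is a wording change in the SAP, and in any matching protocol text. No additional participants or data are needed.
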